### Registration, ethical considerations, and monitoring

The study was registered on ClinicalTrials.gov before the participants’ enrolment started (identifiers: NCT03685214) (Table 1). This study follows the principles of the Helsinki Declaration 2013. The whole protocol has been reviewed and approved by the Ethics Committee of Zhongnan Hospital of Wuhan University (Clinical Ethical Approval No. 2018010) and the Ethics Committee of Wuhan Central Hospital of Tongji Medical College, Huazhong University of Science and Technology (Hospital Ethical Approval No. 201904). An independent data and safety monitoring board (DSMB) is monitoring the progress and safety of the trial. The DSMB is independent of the trial and is comprised of two academic intensivists, professor [name] and professor [name], who are experienced in the conduct of clinical trials in critical illness and outside the study, being able to pause the trial to investigate or give suggestions on potential safety issues to improve our design and implement. The DSMB follows the charter of the Ethics Committee of Zhongnan Hospital of Wuhan University.

**Table 1 Tab1:** Trial registration information

Data category	Information
Primary registration and trial identifying number	ClinicalTrials.gov NCT03685214
Secondary identifying numbers	None
Source(s) of monetary or material support	Wu Jieping Medical Foundation (Project identifier: HRJJ20171026)
Primary sponsor	Zhongnan Hospital of Wuhan University
Secondary sponsor	Wu Jieping Medical Foundation
Contact for public queries	[name]. PhD. [[contact]]
Contact for scientific queries	[name]. PhD. [[contact]]
Public title	Comparison of Balanced Crystalloids and Normal Saline in Septic Patients
Scientific title	Acetate Ringer’s solution versus 0.9% saline for septic patients: study protocol for a multi-center parallel controlled trial
Countries of recruitment	China
Health condition(s) or problem(s) studied	Crystalloid infusion for septic patients
Intervention(s)	Acetate Ringer’s solution versus saline
Key inclusion and exclusion criteria	Inclusion criteria:
	1. At the age of 18 to 80
	2. Diagnosed as sepsis (a possible or specific proof for infection plus Sequential Organs Failure Assessment (SOFA) scores ≥ 2)
	Exclusion criteria:
	1. Patients once having received RRT
	2. Patients requiring RRT prior to enrolment
	3. Patients possessed with only one kidney
	4. Patients with a medical history of renal transplant

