### Study fluid distribution and logistics

Acetate Ringer's soution and saline administered in this trial both have different volume sizes of 250 ml and 500 ml. Components of these two crystalloids are presented (Table 2). The study is an open-label study; thus, the exact solution used is known to investigators, clinicians, and patients. Since the study is non-blind and two fluids used in this study have already been widely applied in the daily care of patients in the above ICUs, there are no problems of logistics.

**Table 2 Tab2:** Components of two crystalloids administered in the trial

Components (mmol/L)	Acetate Ringer’s solution	0.9% saline
Na	140	154
K	4	-
Mg	1	-
Ca	1.5	-
Cl	115	154
Glucose (%)	1	-
Buffer system	Acetate 25	-
Osmotic concentration (mOsmol/kg)	304	286

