### Sample size and statistical power

The sample size was calculated based on the occurrence of MAKE30 on septic patients, which was around 35% [17]. With a noninferiority limit of 1.5%, a total of 312 study participants (156 in each group) would result in a power of at least 80% with a one-sided type-1 error rate (*α*) of 2.5%, allowing a 20% withdrawal rate in each group.

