### Risk evaluation and adverse events

The trial is considered to pose a low risk. Firstly, saline and acetate Ringer’s solution have already been widely used in the clinical practice of ICUs of the above hospitals. Secondly, it still remains controversial which fluid (saline or balanced crystalloid solution) is better for septic patients. Thirdly, clinicians are allowed to make clinical judgments and choose the other crystalloid for a specific patient if they think the assigned one may increase the risk of poor prognosis. Certainly, data of these patients will not be included in the final analysis. Therefore, the adverse events (AEs) of this trial may be minimal.

Still, during the entire observational 28 days from the beginning of the trial, possible AEs will be assessed and recorded in the CRF table. Investigators will evaluate the relationship between the events and our intervention by clinical judgment, and the events will be graded as mild, moderate, and severe. SAEs should be considered if unexpected clinically significant critically ill diseases which may be resulted from fluid intervention happen. AEs, especially SAEs, must be reported to DSMB and followed until they are solved. At the end of the trial, AEs and their relationship to the study will be documented in a table and submitted.

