## Summary/discussion

Fluid resuscitation is the mainstream for the treatment of patients with sepsis/septic shock, and all the guidelines recommend crystalloids as the first choice. Normal saline, a very common crystalloid, poses hyperchloremia and probably worsens AKI which is always complicated by sepsis [26]. However, it is unknown if saline can be safely used in septic patients. Recent studies demonstrated different conclusions in kidney outcomes between saline and balanced solutions in overall critically ill patients [15–17], but showed a significant difference in septic patients by subgroup analysis [16, 17]. This enlightens us to study on a possible dose-response relationship in a high-risk population. Thus, we hypothesize that the harmful effects of saline are associated with the initial kidney function and infused volume of fluids. To confirm this hypothesis, we will carry out this study. As sepsis or septic shock is one of the most typical problems requiring large volume of fluids, this also makes it clinically practically significant to investigate. To our knowledge, this study will be the first to focus on septic patients and compare the effects on outcome between balanced crystalloid solution and saline. In light of this study, a particular comparison will be conducted between acetate Ringer’s solution and saline. Firstly, the patients recruited will be confined to septic/septic shock. Therefore, the conclusions will be applied specifically in septic population. Secondly, the analysis of the association between the due solution and outcome, especially the development of AKI, will be more in details. The infused volume and the baseline renal function will both be taken into consideration. If this trial demonstrates that balanced crystalloid solution or saline shows a priority over the other, it can provide an evidence for the guideline on fluid resuscitation for septic/septic shock. Therefore, the results of this study may be instructive and meaningful.

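### The only stated SAE criterion requires unexpectedness and suspected fluid causality, judged by unblinded staff, so anticipated deaths, new RRT and renal or chloride harm need not be flagged as SAEs

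*Protocol article*

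**What the plan says.** In the protocol article, *Risk evaluation and adverse events* sets the SAE rule: "SAEs should be considered if unexpected clinically significant critically ill diseases which may be resulted from fluid intervention happen". No other SAE criterion appears. The same section says of causality: "Investigators will evaluate the relationship between the events and our intervention by clinical judgment". It also grades AEs as mild, moderate or severe, and directs that "AEs, especially SAEs, must be reported to DSMB and followed until they are solved". It expects little harm: "Therefore, the adverse events (AEs) of this trial may be minimal".

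The term is expanded as severe adverse event in both *Handling of missing data* and *Abbreviations*. *Study fluid distribution and logistics* states: "The study is an open-label study; thus, the exact solution used is known to investigators, clinicians, and patients". *Registration, ethical considerations, and monitoring* describes the DSMB as "being able to pause the trial to investigate or give suggestions on potential safety issues".

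Several harms are anticipated elsewhere. *Study outcomes* puts in-hospital death, new RRT and persistent renal dysfunction in the primary composite, and AKI and electrolyte disturbance among the secondary outcomes. *Summary/discussion* says that saline "poses hyperchloremia and probably worsens AKI which is always complicated by sepsis".

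**The concern.** Whether an event is serious, whether it was expected and whether the treatment may have caused it are three separate questions. The usual order is to settle seriousness from what happened to the patient, and then to record the other two as attributes. Here the last two act as entry conditions and the first is missing. A death in septic shock is neither surprising nor obviously due to the fluid, so a site following the wording has no reason to label it an SAE.

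The causality condition is applied with the fluid known, in a trial that hypothesises harm from saline. Attribution could therefore differ between arms even if true event rates did not, and SAE counts by arm would carry that difference. At stake is how clearly serious events are flagged to the body that can pause the trial, and how far the closing safety table can be trusted.

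**Working it through.** The plan gives no figure for SAEs, so there is none to reproduce. The check is mainly of the text.

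**1. Conditions in the SAE criterion.** The event must be (a) unexpected, (b) a clinically significant critical illness, and (c) possibly caused by the fluid. Death, threat to life, prolonged stay and disability are not mentioned as criteria.

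**2. Anticipated events set against those conditions.**

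| Event | Where it is anticipated | Meets (a)? |
|---|---|---|
| In-hospital death, new RRT, persistent renal dysfunction | Primary outcome; planning rate in *Sample size and statistical power* | Not on an ordinary reading |
| AKI or its worsening | Secondary outcome; *Summary/discussion* | Not on an ordinary reading |
| Hyperchloremia | Secondary outcome; *Summary/discussion* | Not on an ordinary reading |

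The protocol does not define unexpected. The last column is therefore an inference from the protocol's own anticipation of these events.

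**3. Who applies condition (c).** Investigators apply it, by clinical judgment, in an open-label trial.

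**4. Severity against seriousness.** If SAE means an AE graded severe, a severe but expected event is an SAE. Under the stated criterion it is not. The article does not say which reading governs.

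**5. Scale.** The inputs come from *Sample size and statistical power*: a MAKE30 rate in septic patients "which was around 35"%, 312 participants (156 per group) and 20% withdrawal. Expected patients with an event = rate × N.

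- All enrolled: 0.35 × 312 = 109.2, about 109; per arm 0.35 × 156 = 54.6, about 55.
- After 20% withdrawal: 312 × 0.8 = 249.6, and 0.35 × 249.6 = 87.4, about 87.

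So roughly 87 to 109 patients would have a primary-outcome event, none of which has to be classed as an SAE under the stated criterion. This is a count of anticipated events. It does not estimate fluid-related harm, which cannot be derived from the document.

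**The case against.** The strongest reply is that the SAE label sets emphasis and does not control access. The same section sends AEs in general to the DSMB, and has possible AEs recorded over the 28 days and assessed for relationship, which implies that unrelated ones are recorded too. Death, RRT, AKI and electrolyte disturbance are also outcomes compared between groups, so attribution can neither hide nor create an arm difference in them. This stands. A reader might infer that the DSMB never sees these events, and the text does not support that. What remains is narrower: nothing states that outcome events are recorded as AEs, and nothing requires them to be flagged as serious.

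A reader might also set the forecast of minimal AEs against the 35% planning rate and conclude that outcome events are excluded from AE recording. That does not follow. The forecast is a hedged remark about two routinely used fluids, and it sets no counting rule.

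The text says that SAEs should be considered if the conditions hold. It does not say only if. That is fair, but no alternative criterion is offered, and the severity reading is left unreconciled.

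One might try to size the attribution effect by assuming, say, 10% attribution on saline and 2% on acetate Ringer's with equal true rates: 0.10 × 54.6 = 5.5 against 0.02 × 54.6 = 1.1. Those percentages have no source in the document, so the result only returns the assumption. Differential attribution is a possibility here and has not been shown.

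Finally, the timing of DSMB reports is charter material that an article may leave out. That is accepted, and its absence is not part of this point. The SAE criterion itself is stated and badly fixed, so it is not excused as condensed detail.

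**Conclusion.** The point holds in limited form, at moderate severity. The one stated SAE criterion merges seriousness with expectedness and causality, leaves the causality judgment to unblinded investigators, and conflicts with the expansion of SAE as severe. Anticipated major events, on the order of 109 of 312 patients at the planning rate, need not be flagged as SAEs. The consequence is under-flagging and SAE data that depend on attribution. The primary estimate is not affected by this wording, and the DSMB is not shown to be cut off from the events.

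This rests on two assumptions: that the stated criterion is exhaustive, since no other is given, and that events the protocol anticipates are not unexpected. The count also carries the 30-day planning rate over to the 28-day outcome, as the protocol does.

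**What to change.** In *Risk evaluation and adverse events*:

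- Define a serious adverse event by outcome: death, life-threatening event, prolonged hospitalisation or persistent disability, whatever its expectedness or suspected cause. Replace severe with serious in the expansion of SAE.
- Record severity grade, causality and expectedness as separate CRF fields.
- Allow anticipated sepsis and trial-outcome events to be exempt from individual expedited reporting, provided they go to the DSMB as cumulative counts by assigned fluid. The timing can stay in the charter.
- Present the final AE/SAE table by assigned fluid for all enrolled patients. Include those whom a clinician moved to the other crystalloid over concern about prognosis. The section now drops them from the final analysis, although they are the patients in whom harm from the assigned fluid was feared.

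The cost is protocol wording, extra CRF fields and some tabulation, with the counts drawn largely from data already collected. The downside is that more events will be recorded: in septic ICU patients, life-threatening events and prolonged stays are common, so the added recording is more than trivial. The expedited-reporting exemption limits that burden. No treatment rule changes.

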## Summary/discussion

Fluid resuscitation is the mainstream for the treatment of patients with sepsis/septic shock, and all the guidelines recommend crystalloids as the first choice. Normal saline, a very common crystalloid, poses hyperchloremia and probably worsens AKI which is always complicated by sepsis [26]. However, it is unknown if saline can be safely used in septic patients. Recent studies demonstrated different conclusions in kidney outcomes between saline and balanced solutions in overall critically ill patients [15–17], but showed a significant difference in septic patients by subgroup analysis [16, 17]. This enlightens us to study on a possible dose-response relationship in a high-risk population. Thus, we hypothesize that the harmful effects of saline are associated with the initial kidney function and infused volume of fluids. To confirm this hypothesis, we will carry out this study. As sepsis or septic shock is one of the most typical problems requiring large volume of fluids, this also makes it clinically practically significant to investigate. To our knowledge, this study will be the first to focus on septic patients and compare the effects on outcome between balanced crystalloid solution and saline. In light of this study, a particular comparison will be conducted between acetate Ringer’s solution and saline. Firstly, the patients recruited will be confined to septic/septic shock. Therefore, the conclusions will be applied specifically in septic population. Secondly, the analysis of the association between the due solution and outcome, especially the development of AKI, will be more in details. The infused volume and the baseline renal function will both be taken into consideration. If this trial demonstrates that balanced crystalloid solution or saline shows a priority over the other, it can provide an evidence for the guideline on fluid resuscitation for septic/septic shock. Therefore, the results of this study may be instructive and meaningful.

### Trial status

This is the second version of the protocol which was reviewed and approved on April 20, 2018. Patient recruitment has started on March 1, 2019, and will be completed on February 28, 2022.

## Data Availability

The CRFs and final dataset will only be accessible to the study investigators.

## Abbreviations

AKI: Acute kidney injury
ICU: Intensive care unit
ESRD: End-stage renal disease
RRT: Renal replacement therapy
SPLIT: Saline v Plasma-Lyte 148 for Intensive Care Unit Fluid Therapy
SALT: Isotonic Solution Administration Logistical Testing
MAKE: Major adverse kidney events
SPIRIT: Standard Protocol Items: Recommendations for Interventional Trials
KDIGO: Kidney Disease Improving Global Outcomes
DSMB: Data and safety monitoring board
HUS: Hemolytic uremic syndrome
SOFA: Sequential Organs Failure Assessment
eGFR: Estimate glomerular filtration rate
APACHE II: Acute Physiology and Chronic Health Evaluation II
IQR: Interquartile range
CRF: Case Report Format
AE: Adverse event
SAE: Severe adverse event
